### Sample size

Our pilot study revealed an SSI rate of 35 % in patients undergoing colorectal surgery at our institution. Based on previous studies and the clinical experience of the study’s senior investigators, a reduction in the rate of SSI to 20 % (absolute risk reduction 15 %; relative risk reduction 43 %) may be expected. This is the minimum clinically relevant reduction both from a patient outcome perspective and a cost reduction standpoint. Given an alpha of 0.05, for 80 % power, this yields a required sample size of 138 patients per group. The planned sample size will be inflated for potential loss of follow-up, and will be rounded for a final sample size of 150 patients per group and a total study sample of 300 patients. Loss to follow-up is felt to be a minimal concern as patients are required to attend their 30-day post-operative visit to maintain the therapeutic relationship with the surgeon for oncological and disease management.

### Data collection and management

All data collected (baseline characteristics, primary and secondary outcomes) will be recorded through an online data collection portal and be maintained behind a secure server and firewall. Data will be collected by the study nurse, trial personnel and surgical teams. A Data Safety and Monitoring Board (DSMB) will be assembled consisting of three surgeons not involved in patient accrual or in study administration. Given previous demonstration of the safety of iNPWT, we expect minimal to no harm. Accuracy of data collection through the online secure data collection forms will be ensured by the DSMB by performing sample assessments at regular intervals. The severity of adverse events will be evaluated using the Common Terminology Criteria for Adverse Events (CTCAE) v4.0 grading scale (see http://ctep.cancer.gov). Any grade 4 or grade 5 events will be reported to the primary investigator, the DSMB, and the institutional research ethics board as well as the device company headquarters through established reporting systems.

### Statistical analysis

All analysis will be pre-specified and conducted according to the intention-to-treat principle with the use of SPSS version 20 (SPSS Inc., Chicago, IL, USA). The proportion of SSIs amongst all patients undergoing CRR will be compared between the iNPWT and adhesive gauze arms using a chi-square test. An absolute risk increase/reduction for SSI will be presented for the use of iNPWT, as well as the number needed to treat to prevent a single SSI. Data will be analyzed according to the intention-to-treat principle. Patients lost to follow-up will be considered to have developed an SSI for the purposes of primary analysis. Furthermore, despite instructions to contact or return to clinic if any concerns of an SSI arise, any incisions diagnosed or treated for an SSI by any physician will be considered as having had an SSI.

Baseline characteristics of the two groups will be recorded, including body mass index (BMI), self-reported smoking status and co-morbidities. In the event that any of the baseline characteristics are found to differ significantly between the intervention and standard care groups by chance, secondary analyses will be performed using multivariable logistic regression to adjust for the effect of differences in the baseline characteristics on the primary outcome. Results will then be presented as an adjusted odds ratio.

Secondary outcomes will be compared between groups using a chi-square for categorical variables (i.e., need for home care, proportion receiving antibiotics). Non-normally distributed continuous variables (length of hospital stay, duration of home care treatment, number of return visits) will be compared using the Mann-Whitney *U*-test. As potential harm is expected to be minimal, incidence of allergy/sensitivity to iNPWT will be reported, but no formal statistical analyses are planned. A *p*value of less than 0.05 will be considered significant. The trial will undergo only one set of analyses at trial completion. No interim monitoring is planned as, given the small sample size, any interim analysis would have too few events to be interpreted. Recruitment will be completed over 12–16 months, and given that the primary outcome has occurred by 30 days after the last patient is randomized, primary outcome assessment will have occurred by 18 months. Allowing for prolonged data collection for up to 3 months for secondary outcomes, the trial analyses will be completed less than 21 months after the trial commences.

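### Counting every lost patient as an SSI does not fit the 138-to-150 inflation: 80% power holds only up to about 2.3% loss per arm, and unequal loss biases the comparison

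*Protocol article*

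**What the plan says.** The Sample size section takes its control rate, in per cent, from local data: "Our pilot study revealed an SSI rate of 35". For the intervention arm, "a reduction in the rate of SSI to 20 % (absolute risk reduction 15 %; relative risk reduction 43 %) may be expected", and the authors add: "This is the minimum clinically relevant reduction both from a patient outcome perspective and a cost reduction standpoint". The calculation follows: "Given an alpha of 0.05, for 80 % power" the requirement is 138 per group. To allow for losses, this number is then raised and "will be rounded for a final sample size of 150 patients per group and a total study sample of 300 patients". No loss rate is given. The section regards loss as of little worry because patients must return at 30 days for their oncological or disease care.

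The Statistical analysis section makes a chi-square comparison of SSI proportions the primary test, by intention to treat, and reports the absolute risk difference and the number needed to treat (NNT). On missing outcomes it fixes one rule: "Patients lost to follow-up will be considered to have developed an SSI for the purposes of primary analysis".

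**The concern.** The two sections treat lost patients differently. Recruiting extra patients to make up for losses assumes that each loss removes a patient from the denominator. Under the stated rule nobody leaves: each lost patient stays in and is scored as infected. The extra patients therefore replace nothing, while infections that nobody observed enter both arms.

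Two things are at stake. The first is power: false events dilute the difference, and the sample size makes no allowance for that. The second is bias in the primary result. The risk difference and the NNT come from the same coded data, so they move away from the true effect. If loss differs between arms, the rule can create or hide a difference. Patients and surgical teams know the allocation, so equal loss cannot be taken for granted, although outcome assessors are blinded.

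**Working it through.** **Inputs.** From Sample size: 35% versus 20%, alpha 0.05, 80% power, 138 then 150 per group. From Statistical analysis: chi-square test, lost patients counted as SSI. Sidedness of alpha is not stated; two-sided reproduces 138, while one-sided would give 109. Loss rates are assumptions, shown over a range.

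**1. The plan's own figure.** Two-sided, pooled variance, no continuity correction, mean rate 0.275:

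n = [1.960 × √(2 × 0.275 × 0.725) + 0.842 × √(0.35 × 0.65 + 0.20 × 0.80)]² / 0.15² = 137.9, so 138 per group. The figure is correct.

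**2. What the inflation covers.** (150 − 138)/150 = 8%. This is a ceiling, because part of the step is rounding. If 8% were lost and left out, 138 per arm would remain and power would be 80.0%.

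**3. What the rule does.** Let p be the true SSI rate and L the loss fraction, with loss unrelated to arm and to true SSI status. The analysed rate is p(1 − L) + L, which is p plus L(1 − p) false events. The addition is larger in the lower-risk arm. At L = 8%:
- control: 35.0 + 0.08 × 65 = 35.0 + 5.2 = 40.2%
- iNPWT: 20.0 + 0.08 × 80 = 20.0 + 6.4 = 26.4%
- difference: 13.8 points = 15 × (1 − 0.08); NNT 1/0.138 = 7.2 instead of 1/0.15 = 6.7

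**4. Power with 150 per arm, equal loss.** At 8% the mean analysed rate is 0.333, so

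z = [0.138 × √150 − 1.960 × √(2 × 0.333 × 0.667)] / √(0.402 × 0.598 + 0.264 × 0.736) = 0.58, giving power 72.0%.

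| Loss per arm | Analysed rates | Power, lost = SSI | Power, lost left out | n per arm for 80% under the rule |
|---|---|---|---|---|
| 0% | 35.0 vs 20.0 | 83.2% | 83.2% | 138 |
| 2% | 36.3 vs 21.6 | 80.5% | 82.5% | 149 |
| 3% | 37.0 vs 22.4 | 79.1% | 82.1% | 154 |
| 5% | 38.3 vs 24.0 | 76.2% | 81.3% | 165 |
| 8% | 40.2 vs 26.4 | 72.0% | 80.0% | 182 |

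Power crosses 80% at L ≈ 2.3%, which is 0.023 × 150 ≈ 3.5 patients per arm. Exact binomial enumeration of the uncorrected chi-square test agrees: 83.5% at no loss and 72.0% at 8%.

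**5. Unequal loss, no true effect.** With 35% in both arms, the rule alone produces a difference of 0.65 × (control loss − iNPWT loss). Exact two-sided type I error with 150 per arm:

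| Control / iNPWT loss (assumed) | Spurious difference | Type I error |
|---|---|---|
| 0% / 0% | 0 | 4.9% |
| 8% / 8% | 0 | 5.2% |
| 3% / 1% | 1.3 points | 5.5% |
| 5% / 1% | 2.6 points | 7.4% |
| 8% / 2% | 3.9 points | 10.7% |

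In the last row, 10.3% of the 10.7% falsely favours iNPWT.

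**6. Unequal loss against iNPWT, true rates 35% versus 20%.** Exact power is about 72% at 1% (control) versus 3% (iNPWT), 60% at 1% versus 5% and 46% at 2% versus 8%.

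**The case against.** The best defence is that the plan expects very little loss. The 30-day visit is part of routine care, wounds are checked daily after dressing removal and at discharge, and an SSI diagnosed or treated by any physician counts. At 1% to 2% balanced loss power stays above 80%, and at 3% the shortfall is trivial. This stands. A reader might infer that the trial plans for 8% loss and so fails its stated power. The documents do not support that: they give no loss rate, 8% is only the most that 150 could absorb, and the 80% is stated for 138 per group, not for 150 at any given loss.

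It is also fair that the rule is simple, fixed in advance, keeps all randomized patients, and under equal loss errs toward no difference. That stands too, but only for equal loss. Nothing in the document predicts an imbalance, and 8% versus 2% is an extreme case, so the whole range should be read; at 3% versus 1% the type I error barely moves.

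A reader might further infer that a patient who dies without infection is scored as an SSI. The article does not define loss to follow-up or class deaths as lost, so this cannot be concluded.

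Finally, imputation has its own untestable assumption, and sensitivity analyses may well be in an analysis plan that is not shown. Their absence is no finding. The point rests on the primary rule that the article does fix. Intention to treat does not require that rule: it concerns analysis by assigned arm, not the value given to an unobserved outcome.

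**Conclusion.** The concern holds as a conditional mismatch and should be fixed; it is not a fatal flaw. The 138 is right. The allowance for loss and the rule for lost patients do not belong together, so the allowance preserves 80% power only up to about 2.3% loss per arm. Power would be about 76% at 5% and 72% at 8%. The effect on the estimate under equal loss is modest: at 8%, 13.8 rather than 15 points. It does, however, put the expected estimate below the reduction that the plan calls the smallest worth having, even when the true effect equals it.

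These figures assume equal loss, unrelated to true SSI status. If lost patients really had more infections than those followed, the dilution would be smaller. It would go too far to say that the rule inflates the type I error as such: under equal loss the error is kept. Under unequal loss it can rise, or power can fall, depending on which arm loses more, so the rule is not reliably conservative in an open-label trial.

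**What to change.** In the Statistical analysis section, base the primary analysis on SSI status wherever it was observed. Multiply impute unknown 30-day status from arm, site, baseline risk factors and last observed wound status. Keep the present rule as a sensitivity analysis, beside one that counts all lost patients as free of SSI. With 150 per arm this would give roughly 80% power even at 8% loss. The cost is a change of wording and slightly more analysis work, with no extra patients. The downside is reliance on a missing-at-random assumption, which the two sensitivity analyses bracket. Make the change before outcomes are seen by arm, since it can alter the primary result.

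If the rule is kept as primary, state in the Sample size section the assumed loss rate and the power under the rule: 80% only up to about 2.3% loss per arm, and 72% at 8%. Holding 80% power under the rule would need about 165 per arm at 5% loss or 182 at 8%.

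### The secondary adjusted analysis of SSI is triggered by baseline significance tests, so chance imbalance decides whether it is run and what it adjusts for

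*Protocol article*

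**What the plan says.** All of the following is in the protocol article, under Statistical analysis unless noted.

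- The section opens with a general commitment: "All analysis will be pre-specified and conducted according to the intention-to-treat principle".
- The primary comparison of SSI between arms is an unadjusted chi-square test, reported with an absolute risk difference and a number needed to treat (NNT). No condition is attached to it.
- Baseline characteristics are an open list that includes BMI, smoking and co-morbidities. The total number is not given.
- Adjustment is conditional: "In the event that any of the baseline characteristics are found to differ significantly between the intervention and standard care groups by chance", a multivariable logistic regression is added. It is labelled secondary. The next sentence reads "Results will then be presented as an adjusted odds ratio".
- The general significance threshold is p < 0.05. No separate level is given for the baseline comparisons.
- Site is the stratification factor (Study design; Randomization, allocation concealment and blinding). The adjustment rule does not mention it.

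**The concern.** A baseline significance test in a randomized trial tests a null hypothesis that is already known to be true; the protocol itself attributes such differences to chance. The p-value carries no information on whether the factor predicts SSI, and that is what makes adjustment worth doing. A factor unrelated to SSI enters the model if it happens to cross the line. A strong predictor that falls just short is left out.

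At stake is the standing of the adjusted odds ratio. Nobody can say before the arms are compared whether it will exist or which covariates it will contain. If the chi-square result is borderline, a chance-triggered adjusted result could be given more or less weight according to what it shows. The risk is not remote in this field. The Discussion describes an earlier retrospective cohort of this dressing after colorectal resection that found no difference on univariate analysis but a protective effect on multivariate analysis. That study was not randomized, so its adjustment served another purpose, but it shows that adjusted and unadjusted results can be read differently.

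**Working it through.** **1. The plan's own figure.** Inputs from Sample size: "Our pilot study revealed an SSI rate of 35" percent (control); "a reduction in the rate of SSI to 20" percent (intervention); "Given an alpha of 0.05"; 80% power. Sidedness is not stated, and two-sided is assumed.

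With p1 = 0.35, p2 = 0.20 and mean 0.275:

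n = [1.96 × √(2 × 0.275 × 0.725) + 0.8416 × √(0.35 × 0.65 + 0.20 × 0.80)]² / 0.15²
= (1.2377 + 0.5239)² / 0.0225 = 137.9, so 138.

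This matches "this yields a required sample size of 138 patients per group"; a one-sided test would give 109. Analytic power is 80.0% at 138 and 83.2% at 150 per group. The calculation uses no covariates, so the adjustment rule does not touch it.

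**2. How often the trigger fires.** Assumptions: valid randomization, k independent baseline tests, each at 0.05 (the general threshold taken to apply here). The chance of at least one significant difference is 1 − 0.95^k.

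| k (assumed) | Chance that the adjusted model is run |
|---|---|
| 3 | 1 − 0.857 = 14.3% |
| 5 | 1 − 0.774 = 22.6% |
| 10 | 1 − 0.599 = 40.1% |

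Correlated characteristics would change these figures somewhat.

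**3. What the trigger selects.** The plan is for "a final sample size of 150 patients per group and a total study sample of 300 patients". With 150 per arm, a continuous factor such as BMI triggers adjustment when the arm means differ by about 1.96 × √(2/150) = 0.23 SD. A strong predictor of SSI imbalanced by 0.20 SD would be left out. A factor with no relation to SSI imbalanced by 0.25 SD would be adjusted for.

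**4. What fixed adjustment would change.** The documents give no prognostic strength, so this is a range under assumption: three independent covariates with equal odds ratio per SD, marginal SSI rates held at 35% and 20%, 150 per arm, 4,000 simulated trials per scenario (Monte Carlo standard error about 0.6 points).

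| Odds ratio per SD (assumed) | Chi-square | Fixed adjustment | Triggered adjustment |
|---|---|---|---|
| 1.0 | 82.7% | 82.1% | 82.7% |
| 1.3 | 84.1% | 84.4% | 83.9% |
| 1.6 | 84.4% | 87.7% | 84.7% |
| 2.0 | 83.0% | 89.9% | 83.4% |

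The trigger fired in 14 to 15% of simulated trials, as step 2 predicts for k = 3, and gave essentially the power of no adjustment. Fixed adjustment gained about 0 to 7 points. With no treatment effect, the triggered procedure applied mechanically rejected in 4.4 to 5.3% of trials. In the strongest scenario the fixed-adjustment Wald test rejected in 5.95% and the chi-square test in 5.4%, so a small part of the 7 points may come from a slightly liberal test.

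**5. Scale.** At the design rates the risk difference is 15 points (NNT 1/0.15 = 6.7). The odds ratio is (0.20/0.80)/(0.35/0.65) = 0.46. An adjusted odds ratio alone cannot be set directly against the primary risk difference and NNT.

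**The case against.** The strongest defence is that the rule governs only a secondary analysis. The primary test is fixed, unconditional and unadjusted, which is a legitimate choice, and its type I error and power do not depend on the trigger. That stands, and it limits the point.

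Three stronger readings are tempting and are not supported.

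- **The rule contradicts the pre-specification statement.** A reader might set "All analysis will be pre-specified and conducted according to the intention-to-treat principle" against a data-dependent model. But a conditional rule written in advance is itself pre-specified, and the covariate list may be in an analysis plan that is not shown. What remains is that the rule leaves the model's existence and content to the data. That is a weakness of the stated rule, not a plain contradiction.
- **The trial loses power.** The primary conclusion rests on the chi-square test, whose power stays the same whether or not a secondary model is fitted. A gain for the adjusted analysis needs prognostic covariates, and the documents give no figure for their strength. For weak covariates the gain is about zero.
- **The adjusted and primary results cannot be compared at all.** The crude odds ratio follows from the same two proportions, and an odds ratio is the usual output of logistic regression. The difference of scale is minor and easily remedied.

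It can also be said that 14 to 40% rests on an assumed number of independent tests. That is true; for three tests, one for each item named, it is 14%. The criticism of the trigger does not depend on the exact figure.

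**Conclusion.** The point holds in a limited form. The protocol states a poor rule: baseline significance tests decide whether the secondary adjusted analysis of SSI is run and which factors it contains. Under randomization this is selection by chance imbalance and not by prognostic value. Under independence and a 0.05 level, the model would appear in 14% (k = 3) to 40% (k = 10) of trials.

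The consequence is a secondary result that depends on the data and is open to selective emphasis. The primary result is not biased, no error rate of the primary test is inflated, and the sample size is not wrong. The choice of trigger is clearly unsound. How much precision the secondary analysis forgoes cannot be derived from the documents.

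**What to change.** In Statistical analysis:

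1. Delete the significance-test trigger. Describe baseline characteristics by arm without tests.
2. Fix before analysis a short covariate set from data the trial already has: site (as stratification factor), BMI, smoking and recorded co-morbidities, with the coding of co-morbidities stated. Diabetes and a co-morbidity score are not named in the article as collected, so they should be listed only if they are. At the design rates about 150 × 0.35 + 150 × 0.20 = 82.5 events are expected, which is a reason to keep the set short.
3. Fit the secondary logistic model whatever the observed balance, and report it whatever it shows.
4. Beside the adjusted odds ratio, report a standardized risk difference with 95% CI, so that it can be read against the primary risk difference and NNT.

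The chi-square test stays primary. The change needs no further patients, visits or data. Its cost is a wording change and slightly more analysis work.

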## Discussion

The NEPTUNE trial is the first randomized controlled trial to investigate the role of iNPWT in reducing the incidence of SSIs in elective, open, CRR. Only one other study has been performed investigating the role of iNPWT following a CRR using a retrospective cohort design. Bonds et al., used iNPWT in patients following a CRR, at the request of the operating surgeon [17]. Although no difference was reported on univariate analysis, the use of iNPWT was found to be protective for SSI on multivariate analysis after controlling for various risk factors. Despite the positive findings and adjustments made, a significant selection bias exists in this study, and a randomized controlled trial is warranted. It is anticipated that the NEPTUNE trial will assist in the development of consensus recommendations for the use of iNPWT in patients following a CRR.

There are multiple theorized benefits of iNPWT in decreasing SSI rates. In a study by Wackenfors et al., laser Doppler velocimetry was used to assess the vascularity of incisions in a porcine model with NPWT. Increases in tissue microvascular perfusion were seen to correlate with the pressure applied in addition to increases in the partial pressure of oxygen within the soft tissue environment [18]. Other porcine models have demonstrated reduced rates of hematoma and serum formation in addition to increased lymphatic fluid clearance [19]. This is also associated with decreased shear forces and stresses as the negative pressure environment maintains tissue apposition. Incisional NPWT devices decrease the lateral stresses placed on incisions by approximately 50 %, leading to a distribution more consistent with that of intact tissue and further increases the force required to disrupt the incision [20]. The closed suction environment placed under sterile conditions also effectively separates the incision from the surrounding environment, thus theoretically preventing the inoculation of environmental bacteria.

This design of this trial will allow for strong conclusions to be made as to the role of iNPWT after CRR. The major limitation of this trial is in the inability to completely blind members of the clinical team, and the patient, to the treatment arm. Placebo control is not felt to be possible, as any additional dressing placed over the surgical wound may alter wound healing mechanics, and, therefore, likely impact on the rate of SSI. The idea of a “sham device” was initially entertained, but given the pragmatic nature of this trial, this or any alternate dressing would further fail to represent the current standard of care and use may result in misleading conclusions.

The results of this trial will be used to determine the role of iNPWT in the prevention of SSI after colorectal surgery. If this intervention is shown to be effective for the prevention of SSI in this high-risk population, significant benefit with respect to both patient morbidity and resource utilization may be achieved.

